##### Symptoms of anxiety and depression

Symptoms of anxiety and depression will be measured with the Danish translation of the Hospital Anxiety and Depression Scale. The scale consists of two subscales for anxiety and depression. The subscales range from 0 to 21, and a high score indicates a high symptom level [81].

#### Secondary outcomes: physical measurements and physical performance tests

##### Body mass index

Body mass index will be calculated as body weight (kg) divided by squared height (m). Height will be measured to the nearest 0.5 cm using a Seca 222 stadiometer.

##### Maximal mouth opening

To assess trismus, maximal mouth opening will be measured in mm using a TheraBite® Range-Of-Motion ROM Scale. Participants will be seated on a chair during the test. The notch of the scale will be placed on the left lower front tooth, and the participant will be asked to open the mouth as widely as possible without discomfort. While still touching the lower front tooth, the scale will be rotated until it also touches the left upper front teeth, and the measuring point will be registered. Three measurements will be performed, and the highest measurement will be used for data analyses.

##### Hand grip strength

Hand grip strength will be measured in kg using a calibrated Jamar hand dynamometer. The measurement protocol is based on recommendations from Roberts et al. [82]. Measurements will be made with the hand dynamometer in the second handle position. Three consecutive measurements in each hand will be performed, and the highest measurement for each hand will be used for data analyses.

##### 30-second chair stand test

The 30-second chair stand test assesses lower body strength [83]. It measures the number of times a person can sit and rise to full standing position from a chair in 30 s. The test protocol follows the method described by Jones et al. [83]. The participant will be instructed to be fully seated between the stands and encouraged to complete as many full stands as possible during the 30 s without using their hands. The final score will be the total number of stands executed correctly. If participants are unable to rise without using their hands, it will be registered that the test is completed in a modified version.

##### 6-minute walk test

The 6-minute walk test is considered a measure of the submaximal level of functional capacity [84].

The test will be performed on a 30-m walking course. Participants will be instructed to walk as many laps as possible during the six minutes without jogging or running. Each minute, the tester will inform the participant about the remaining time, but otherwise the test will be performed in silence. After six minutes, the participant will be asked to stop, and completed distance of the final lap will be measured to the nearest metre. The score will be the total distance walked in metres.

### Sample size

The sample size calculation is based on quantitative data from the previous pilot study [4]. The mean weight change in percent was 1.74 ± 2.37 when restricting to participants with cancer of the pharynx, larynx, or oral cavity and who had completed radiation therapy 1–5 years prior to participation. Based on these data, 30 participants are required in each group to achieve a power of 80% and a significance level of 5%. Thus with an estimated withdrawal rate of 15% [4], we will include 36 participants in each group.

### Data analysis

The statistical analysis plan for the trial is shown in Additional file 5. Data will be analysed in SAS® Enterprise Guide® 7.1 by both per protocol and intention-to-treat principle [85]. Data analyses will not be commenced until all data collection is completed. A blinded researcher ([name]) will analyse the data, and the project group will interpret results before unblinding. Development in outcome scores from baseline to 3-month follow-up will be calculated for each participant, and differences between intervention group and wait-list control group will be tested using a two-sample two-sided t-test for normally distributed data and Mann-Whitney U test for non-normally distributed data. A significance level of 5% will be applied. Effect size will be estimated with Cohens d [86]. Multiple linear regression will be used to assess the influence of potential confounding variables (e.g. time interval from completion of treatment) on intervention effect. Mean baseline values for outcome scores in both groups will be presented in result tables. Simple linear regression will be used to test correlations between developments in outcome scores and baseline scores in NRS 2002, MDADI or PG-SGA SF. Sensitivity, specificity and predictive values of different cut-offs in NRS 2002, MDADI or PG-SGA SF at baseline in relation to a clinically relevant improvement in outcome scores during participation in the programme will be assessed. To avoid missing data, participants who drop out of the trial will be encouraged to participate in follow-up measurements. The percentage and patterns of missing values in outcome variables will be examined. If data are missing at random and the percentage of missing data is not substantial [87], multiple imputation techniques will be used in the intention-to-treat analyses.

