**Fig. 2 Fig2:**
[figure not shown]
Flow chart of the NUTRI-HAB trial

Randomisation will be stratified by need for rehabilitation services measured by the REHPA scale adapted from the National Comprehensive Cancer Network® Distress Thermometer [72]. On the REHPA Scale, participants indicate how close or how far they are from living the life they want after or in spite of their disease. A higher score indicates greater rehabilitation needs. The REHPA Scale was included in the nationwide survey. A certain score on the REHPA scale is not an inclusion criteria for the present trial, but randomisation will be stratified to ensure similar proportions of individuals with a score of ≥3 across the invitation lists. Participants will be randomised in STATA/IC 15.1 by a blinded researcher ([name]) who is not involved in the trial intervention or assessment of outcomes.

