#### Primary outcome

The primary outcome is percentage change in body weight from baseline to 3-month follow-up. Body weight will be measured to the nearest 0.1 kg on calibrated Seca 877/878 scales. In accordance with National Institute for Health Research Southampton Biomedical Research Centre Procedure for Measuring Adult Weight [76], body weight measurements will be continued until three consecutive measurements within 100 g of each other are obtained. The mean of the three will be used in the analyses. Participants will be asked to limit their food and fluid intake two hours before the weighing and to empty their bladder immediately before. For each participant, body weight measurements will be performed at the same time of day (before/after noon) at baseline and 3-month follow-up.

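### The between-arm test has neither baseline value nor REHPA stratum as a covariate, and the data decide whether it compares means or ranks

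*Protocol article*

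**What the plan says.** Primary outcome section: "The primary outcome is percentage change in body weight from baseline to 3-month follow-up".

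Data analysis section: "Development in outcome scores from baseline to 3-month follow-up will be calculated for each participant", and differences between the two groups "will be tested using a two-sample two-sided t-test for normally distributed data and Mann-Whitney U test for non-normally distributed data". Cohen's d is the planned effect size.

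Inclusion and randomisation section: "Randomisation will be stratified by need for rehabilitation services measured by the REHPA scale", and more precisely "randomisation will be stratified to ensure similar proportions of individuals with a score of ≥3 across the invitation lists". The REHPA scale is not mentioned in the Data analysis section.

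Covariates enter only in a separate step: "Multiple linear regression will be used to assess the influence of potential confounding variables (e.g. time interval from completion of treatment) on intervention effect". For baseline values the section adds only that "Mean baseline values for outcome scores in both groups will be presented in result tables".

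The Data analysis section refers to a statistical analysis plan in Additional file 5, which is not available here.

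**The concern.** There are two issues.

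**Covariates.** The randomisation is stratified, but the test that judges the treatment effect does not use the stratum. Baseline enters through the change score but not as a covariate. Both variables are already collected. If either predicts the outcome, its variation stays in the error term, and chance differences at baseline stay in the estimate.

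**Estimand.** The t-test compares means and the Mann-Whitney test compares ranks. If the observed distribution selects the test, it also selects what the trial estimates, including for the primary outcome. The rest of the plan is built on means: the sample size uses a mean and SD, and Cohen's d is a standardised mean difference. Across many bounded questionnaire scales, the results could become a mixture of the two kinds of comparison.

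At stake are precision and interpretability, not false-positive control.

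**Working it through.** **1. The plan's own figure.** Inputs from the Sample size section: difference 1.74, SD 2.37, two-sided 5%, power 80%, withdrawal 15%.

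n per arm = 2(1.96 + 0.8416)² × 2.37² / 1.74² = 29.1, rounded up to 30. The noncentral t solution is 30.1, with power 0.798 at 30. Allowing for withdrawal, 30 / 0.85 = 35.3, rounded up to 36. Both stated figures reproduce, and they belong to an unadjusted comparison of means.

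**2. Leaving out the stratum.** The documents do not say how strongly REHPA ≥3 predicts weight change, so stratum R² is an assumed range. The simulation used 30 per arm, normal errors, SD 2.37, strata perfectly balanced between arms and half of participants in each stratum (assumed), with 5,000 null and 2,500 alternative runs per setting.

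| Stratum R² | Type I error, unadjusted t | Type I error, adjusted | Power, unadjusted t | Power, adjusted |
|---|---|---|---|---|
| 0 | 0.050 | 0.050 | 0.79 | 0.79 |
| 0.10 | 0.039 | 0.048 | 0.81 | 0.85 |
| 0.30 | 0.018 | 0.043 | 0.82 | 0.91 |

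The unadjusted test becomes conservative as the stratum becomes prognostic. Adjustment costs nothing here when the stratum is irrelevant.

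As a cross-check with residual SD = 2.37 × √(1 − R²), the step 1 formula gives 30, 27 and 21 per arm at R² of 0, 0.10 and 0.30.

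**3. Leaving out baseline, for outcomes analysed as absolute change.** Take equal variance at both visits (set to 1) and correlation r. The change score has variance 2(1 − r) and the ANCOVA residual has variance 1 − r². The ratio is (1 − r²) / [2(1 − r)] = (1 + r)/2. The documents give no r, so the range is assumed.

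| r | Variance ratio, ANCOVA to change score | Reduction |
|---|---|---|
| 0.5 | 0.75 | 25% |
| 0.7 | 0.85 | 15% |
| 0.8 | 0.90 | 10% |
| 0.9 | 0.95 | 5% |
| 0.98 | 0.99 | 1% |

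This formula does not describe the primary outcome, which is a percentage change and so is already scaled by baseline weight. Body weight over three months is also likely to be very highly correlated, so the gain there is probably small.

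**4. Choosing the test by distribution.** The simulation also ran a version in which a Shapiro-Wilk test in each arm selected the t-test or Mann-Whitney. Across normal, t (3 df) and exponential errors, and all three R² values, type I error was at most 0.051. The switch does not inflate false positives. What it leaves unfixed is the quantity being estimated.

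**The case against.** **Baseline is used.** Each test works on change from baseline, and the primary outcome is a percentage of it. This is correct. A reader might infer that the plan ignores baseline, but the documents support only the narrower statement that baseline is not a covariate.

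**The error rate is protected.** Both tests and the condition for choosing between them are named in advance. Analysis waits until data collection is complete, the analyst is blinded, and results are interpreted before unblinding. A reader might infer that the switch opens the trial to false positives or to favouring an arm. Step 4 and these safeguards do not support that. Blinding does not fix the estimand, however.

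**Rank tests can be adjusted.** The van Elteren test is a stratified form of the Mann-Whitney test, and a Hodges-Lehmann shift can accompany a rank test. This is also correct. The objection is to the test as planned, which is unstratified.

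**A mean-based model can lose power.** In the same simulation with t (3 df) errors and an irrelevant stratum, the distribution-based choice had power 0.95, against 0.83 for the stratum-adjusted linear model. With exponential errors the figures were 0.95 and 0.81. Adding the covariates costs nothing, but giving up the rank test has a price if changes are heavily non-normal. This supports keeping the rank test as a sensitivity analysis. It does not justify letting the data choose the primary estimand.

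**The analysis plan may say more.** The example in the regression sentence marks an open list, and Additional file 5 may give the covariates and a normality criterion. Their absence from the article is no fault. But the article itself states the between-arm test, and the regression stands apart from it.

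**Conclusion.** The point holds as a matter of efficiency and of a fixed estimand. The stated test omits the stratification factor and the baseline covariate, and the observed distribution decides whether means or ranks are compared. It does not invalidate the trial: type I error is not inflated, and 30 and 36 per group remain correct for the stated test.

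The size depends on quantities that the documents do not give. For the stratum, the power forgone at 30 per arm is nil at R² = 0, about 0.03 at R² = 0.10 (0.846 − 0.814) and about 0.09 at R² = 0.30 (0.911 − 0.821), with normal errors. For baseline in the secondary outcomes, the variance reduction runs from 25% at r = 0.5 to 1% at r = 0.98. A reader might carry the upper end over to body weight, but neither the formula nor the likely correlation supports that.

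The simulation assumed perfect stratum balance. In the trial, stratification is applied to the invitation lists, before people accept or decline, so balance among participants is not guaranteed. This is a further reason to adjust.

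**What to change.** - **Primary analysis:** one linear model of percentage weight change on arm, baseline weight and REHPA stratum (≥3 versus <3), reporting the adjusted mean difference with its 95% confidence interval.
- **Continuous secondary outcomes:** the 3-month value on arm, its own baseline value and REHPA stratum.
- **Inference:** fix one method in advance for all outcomes, for example a bootstrap confidence interval for every outcome, so that it does not depend on a look at the distribution.
- **Sensitivity analyses only:** the unadjusted t-test and the Mann-Whitney test or its stratified form.

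The cost is wording in the Data analysis section and, where needed, in the analysis plan. Baseline outcomes and the REHPA score are already collected, and the sample size need not change.

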**Methods:**

In a randomised controlled trial, 72 patients treated for HNC recruited through a nationwide survey will be randomised to a multidisciplinary residential nutritional rehabilitation programme or to a wait-list control group. Data are collected at baseline, three and six months. Primary outcome is change in body weight, and secondary outcomes include changes in quality of life, physical function and symptoms of anxiety and depression. Potential correlations between intervention effect and baseline scores in NRS 2002, PG-SGA-SF and MDADI will be tested, and sensitivity, specificity and predictive values of the three tools in relation to a clinically relevant improvement in outcome scores will be assessed.

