The increasing population of patients treated for HNC may present a challenge to existing health care systems through increased rehabilitation costs. Residential rehabilitation programmes and other specialised rehabilitation services aimed at eating problems may be costly, and may not be indicated for all patients treated for HNC. Systematic screening and/or assessment of rehabilitation needs in patients treated for HNC may optimise the use of existing resources while ensuring referral to appropriate rehabilitation services for those in need.

The European Society for Clinical Nutrition and Metabolism recommends that nutritional screening is performed at cancer diagnosis and repeated regularly depending on the stability of the clinical situation [24]. Several tools have been developed to screen and assess nutritional risk, nutritional status and nutrition impact symptoms [24–28]. Nutritional Risk Screening 2002 (NRS 2002), [26] is validated to identify patients, regardless of their diagnosis, who will benefit from nutritional intervention. Yet, to our knowledge no studies have validated NRS 2002 in patients treated for HNC after treatment, and even for patients with HNC prior to treatment, it has been suggested to use a modified version with a different cut-off value [29]. Furthermore, NRS 2002 only assesses dietary intake as the consumed amount in relation to requirements [26]. It does not assess nutrition impact symptoms, which would be highly relevant in this population. The Scored Patient-Generated Subjective Global Assessment Short Form (PG-SGA SF) includes information on nutrition impact symptoms and changes in dietary intake (amount or consistency) in the assessment of nutritional risk and nutritional deficit [27], but no validation studies have been carried out in patients after treatment for HNC. The M. D. Anderson Dysphagia Inventory (MDADI) [28] is developed to assess dysphagia-specific QOL in patients with HNC. But so far, no clinical studies have investigated associations between MDADI score and intervention effect. Hence, the evidence is scarce on the three tools’ ability to identify patients treated for HNC who will benefit from posttreatment nutritional rehabilitation.

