### Trial objectives

The objectives of the trial are:
To test the effect of a multidisciplinary residential nutritional rehabilitation programme compared to standard care on the primary outcome body weight and secondary outcomes health-related QOL, physical function and symptoms of anxiety and depression in patients curatively treated for HNCTo test for correlations between participants’ development in outcome scores during their participation in the programme and their baseline scores in NRS 2002 [26], PG-SGA SF [27], and MDADI [28] and to assess sensitivity, specificity and predictive values of the three tools in relation to a clinically relevant improvement in outcome scores

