#### Nutritional risk and presence of nutrition impact symptoms at entry of the rehabilitation programme

##### Nutritional risk screening 2002

The NRS 2002 has been developed and validated to identify admitted patients who will benefit from nutritional intervention [26]. Screening with NRS 2002 comprises a primary screening and, dependent on the result, a secondary screening. The primary screening assesses the presence of recent weight loss, body mass index < 20.5, decreased dietary intake in the preceding week and severe disease. In the secondary screening, the overall score comprises an A-score for nutritional status, a B-score for disease severity and an extra point if aged 70 or above. A higher score indicates greater nutritional risk [26]. Hence, questions on recent changes in body weight and dietary intake will be included in the questionnaire.

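### The screening-tool analysis is presented as showing who benefits from the programme, but it regresses change on baseline score with no control-arm contrast

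*Protocol article*

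**What the plan says.** The protocol article describes the tool analysis in two ways.

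- **As a question about benefit.** The Background says that evidence is scarce on the three tools' "ability to identify patients treated for HNC who will benefit from posttreatment nutritional rehabilitation". The Methods part of the abstract says: "Potential correlations between intervention effect and baseline scores in NRS 2002, PG-SGA-SF and MDADI will be tested". The Discussion, in the abstract and in the closing paragraph of the main text, says the trial will inform how nutritional rehabilitation should be selected and prioritised.
- **As a question about change.** Trial objectives, second objective, relates participants' "development in outcome scores during their participation in the programme and their baseline scores in NRS 2002" and the other two tools. Data analysis implements this: "Simple linear regression will be used to test correlations between developments in outcome scores and baseline scores in NRS 2002, MDADI or PG-SGA SF". The cut-offs are then judged "in relation to a clinically relevant improvement in outcome scores during participation in the programme will be assessed".

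The control arm appears in Data analysis for the first objective, where "differences between intervention group and wait-list control group will be tested using a two-sample two-sided t-test" (or a Mann-Whitney test). The only other model named is: "Multiple linear regression will be used to assess the influence of potential confounding variables (e.g. time interval from completion of treatment) on intervention effect". The tools are not named there, and no arm-by-tool term is stated.

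**The concern.** Benefit is the difference between what happens with the programme and what would have happened without it. A one-predictor regression of change on baseline score does not estimate that difference. Neither do accuracy measures whose reference standard is a person's own improvement.

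By the article's own descriptions, NRS 2002 covers recent weight loss and reduced intake. PG-SGA SF covers weight change, intake and symptoms, and MDADI is a dysphagia-specific quality-of-life score. The outcomes include weight and quality-of-life scales. A tool that shares temporary variation with the baseline outcome will correlate with later change even if the programme does nothing.

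The protocol accepts the principle elsewhere: the Background says that improvements in the uncontrolled pilot need a randomised test. If the tool results are then used to prioritise places, a tool could be adopted because it marks people whose scores would have moved anyway.

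**Working it through.** **The plan's own figure.** Sample size gives a mean change of 1.74, an SD of 2.37, 80% power and 5% significance. n = 2 × (1.96 + 0.84)² × 2.37² / 1.74² ≈ 29.1, so 30 per group; 30 / 0.85 = 35.3, so 36. The figure reproduces, but it serves Objective 1. No figure is given for Objective 2, so the inputs below are assumptions shown as ranges.

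**Model with no treatment effect.** Let the outcome be a stable true score plus independent error at each visit, with reliability ρ, which is also the baseline-to-3-month correlation. Let the tool correlate q with the observed baseline outcome and relate to follow-up only through it. The size of the expected tool-change correlation is then

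r = q(1 − ρ) / √(2(1 − ρ)) = q√((1 − ρ)/2).

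- ρ = 0.9, q = 0.3: r = 0.3 × √0.05 = 0.067
- ρ = 0.7, q = 0.5: r = 0.5 × √0.15 = 0.194
- ρ = 0.6, q = 0.7: r = 0.7 × √0.20 = 0.313

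**Simulation of that model** (30 per arm, 4,000 runs per scenario, nominal 5%):

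| ρ | q | Simple regression, programme arm | Arm-by-tool interaction, both arms |
|---|---|---|---|
| 0.9 | 0.3 | 6.5% | 4.8% |
| 0.7 | 0.5 | 18.0% | 5.2% |
| 0.6 | 0.7 | 40.6% | 4.6% |

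Over the full grid of ρ from 0.6 to 0.9 and q from 0.3 to 0.7, simple regression ran from 6.5% to 40.6% and the interaction test from 4.6% to 5.3%. The interaction was fitted to change scores, without further baseline adjustment.

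**Cut-offs under the same null.** With ρ = 0.7, q = 0.5, a median cut-off and improvement defined as at least 0.5 SD, 26% of people improve. The tool shows sensitivity 60%, specificity 53% and positive predictive value 31%, although nobody benefits.

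**Body weight separately.** Assume body weight has a between-person SD (S) of 10% to 20% of the mean. The pilot SD of change implies 1 − ρ = 2.37² / (2S²).

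- S = 10: 5.617 / 200 = 0.028, so ρ ≈ 0.97; with q = 0.7, r = 0.7 × √0.014 ≈ 0.083
- S = 20: 5.617 / 800 = 0.0070, so ρ ≈ 0.99; with q = 0.5, r = 0.5 × √0.0035 ≈ 0.030

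By the Fisher z approximation, P(p < 0.05) = 1 − Φ(1.96 − z√(n − 3)) + Φ(−1.96 − z√(n − 3)), where z = atanh r. At n = 30 this gives 7.2% for r = 0.083 and 5.3% for r = 0.030; at n = 36 the larger figure is 7.7%. So the range is about 5% to 8%.

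**Precision of the controlled test.** An interaction is a difference of two independent slopes. With equal arms its standard error is √2 ≈ 1.4 times that of a single-arm slope.

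**The case against.** **Objective 2 is worded as a correlation with change, and the analysis answers that.** This is right. A reader might infer that the objective itself asks who benefits; its text does not. The defect is a mismatch between the objective and analysis on one side and the abstract, Background and Discussion on the other. Consistent prognostic wording would remove the mismatch, though the benefit question would then go unanswered.

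**The size rests on assumptions.** This also stands. No document figure fixes the reliabilities or correlations. The bias vanishes if a tool tracks only the stable true score. Participants are 1 to 5 years past radiotherapy with problems that may be chronic, so spontaneous improvement may be modest; natural course was not simulated. A reader might carry the upper figures over to body weight, but the pilot SD does not support that.

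**The statistical analysis plan (Additional file 5), not available here, may add an interaction.** It may. The article nevertheless names simple linear regression, and its abstract labels the result as intervention effect. If the quoted sentence is meant to pool both arms, it still contains no contrast between them.

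**Wait-list timing.** From the heading "Nutritional risk and presence of nutrition impact symptoms at entry of the rehabilitation programme" a reader might infer that the wait-list arm's trial baseline will stand in for its score at programme entry, about three months later. No section says so. Table 2 schedules the tools again at 3 months, and Trial design treats the data up to 6 months as exploratory.

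**Conclusion.** The concern holds as a mismatch between claim and analysis. As written, the tool results can show association with change but cannot show who benefits, and the article presents them as doing the latter.

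For patient-reported outcomes with reliability 0.6 to 0.9 and tool-outcome correlation 0.3 to 0.7 (both assumed), a programme with no effect would still yield a significant tool association in about 6.5% to 41% of trials, against about 5% for a controlled interaction test. For body weight, regression to the mean alone gives about 5% to 8%. That figure excludes any recovery after recent weight loss.

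The randomised comparison for Objective 1 is unaffected. A reader might conclude that the interaction must become the main analysis of Objective 2. The documents do not support that: the trial was not sized for it, and it would be imprecise with 72 participants. This is a point that should be fixed, not one that undermines the trial.

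**What to change.** 1. In Data analysis, add a model on the randomised baseline-to-3-month data from both arms: 3-month outcome on baseline outcome, arm, tool score and arm × tool score. Label it exploratory.
2. For each cut-off, report the proportion improved in each arm, above and below the cut-off, with the between-arm difference.
3. Describe the single-arm regression and the sensitivity, specificity and predictive values as prognostic only.
4. Change the intervention-effect wording in the abstract's Methods, and the selection and prioritisation statement in the Discussion (abstract and main text), to match.

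Cost: wording and a modest amount of extra analysis. Table 2 already schedules the tools at baseline and the outcomes at baseline and 3 months, so no new data are needed. The price is imprecision: interaction estimates across three tools and many outcomes will have wide intervals and should be reported as such.
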